## Abstract

**Introduction:**

Depression is a common non-motor symptom of Parkinson’s disease (PD), which seriously affects the quality of life of patients with PD. The main clinical treatment method for depression in Parkinson’s disease is medication treatment. However, the medication treatment has a long cycle and many adverse reactions. Acupuncture as a non-pharmacological intervention method, has been widely used in the treatment of patients with Parkinson’s disease and depressive disorders in China. Therefore, the study of acupuncture in the treatment of early Parkinson’s disease with mild to moderate depression has important practical significance.

**Methods and analysis:**

In this randomized, single-blinded, and placebo-controlled study, a total of 88 patients with depression in Parkinson’s disease (DPD) will be randomly allocated to either an acupuncture group or a control group in parallel in a 1:1 allocation ratio. Each group will receive 30 min acupuncture treatments or sham acupuncture treatments, 3 times a week, for 12 weeks, followed by a 36-week follow-up period. The primary outcome is the response rate of the Hamilton Depression Rating Scale-17 at 12 weeks. Data will be collected at baseline, at the end of the 12-week treatment period, and during the 12-week and 36-week follow-up.

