## Introduction

Parkinson’s disease (PD) is a neurodegenerative disease characterized by bradykinesia, rest tremor, and muscle stiffness (1, 2). In addition to symptoms of movement disorders, PD patients also experience various non-motor symptoms, such as depression, rapid eye movement sleep behavior disorder, pain, etc. (3). Approximately 35 to 50% of PD patients will experience depression, which often persists (3, 4).

Depression is a common non-motor symptom that occurs in patients with all stages of PD (5). A meta-study showed that 17% of PD patients in clinical practice suffer from severe depression, 35% have clinically significant depressive symptoms (6), and a portion of patients have suicidal tendencies (7). Depression is one of the biggest factors affecting the quality of life of PD patients, especially female PD patients (8).

In addition, depression is often a sign of other symptoms of PD and has diagnostic value. For early PD patients, depression may be one of the early signs before the onset of motor symptoms (9). For patients with advanced PD, depression may be one of the early signs of more severe non-motor symptoms (dementia, falls, disability) in the later stages (10, 11). Secondly, depression itself can seriously affect the quality of life of Parkinson’s disease patients. Patients with Parkinson’s disease and depression often experience significant negative emotions such as shame, suicidal tendencies, low morale, and despair, and a considerable number of patients die by suicide (12). These negative emotions seriously affect the quality of life (QoL) of Parkinson’s disease patients and significantly impact prognosis (13, 14). Therefore, developing a new treatment plan for Parkinson’s disease with depression has practical significance and can improve the quality of life of patients.

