## Methods

### Study design

The methodological framework for this project was developed based on the Consolidated Standards of Reporting Trials (CONSORT) statement for non-pharmacological interventions. The protocol was approved by the Medical Ethics Committee of the Beijing Hospital of Traditional Chinese Medicine (2023BL02-013-01) and is registered with the Chinese Clinical Trial Registry (Registration No. ChiCTR2300069310).

This trial is a 1:1 randomized, single-blind, and placebo-controlled study with two parallel groups, involving patients with early PD with mild to moderate depression. The study is designed to evaluate the effect and neural mechanism of acupuncture treatment on depression and motor symptoms after a 12-week intervention period. As shown in Figure 1, depression assessments and MRI scans will be performed immediately after baseline and intervention completion. The enrollment schedules, interventions, and assessments are summarized in Table 1.

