### Exclusion criteria

Patients with secondary Parkinson’s syndrome or Parkinson’s superposition syndrome.Patients who are currently taking or have taken traditional antidepressants in the past 2 weeks, such as selective serotonin and norepinephrine reuptake inhibitors (venlafaxine, etc.), selective serotonin reuptake inhibitors (sertraline, paroxetine, fluoxetine, citalopram, etc.), tricyclic antidepressants (amitriptyline, etc.).Patients undergoing neurosurgical surgery (deep brain stimulation), psychological therapy, or repeated transcranial magnetic stimulation therapy.Patients with serious internal medical conditions such as heart, liver, kidney, hematopoietic system disorders malignant tumors, as well as mental disorders.Patients are unable to undergo an fMRI scan for other reasons.

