##### Secondary indicator

The change from baseline in resting-state fMRI (at week 12). The response rate of HAMD-17 (at weeks 24, and 48). The changes from baseline in UPDRS-III and PDQ-39 (at weeks 12, 24, and 48). The response rate of QIDS-SR, and the change from baseline in PDQ-39 (at weeks 12, 24, and 48). The proportion of patients with progression≥0.5 grades compared to the baseline of H–Y staging (at week 48).

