### Safety assessments

Any adverse effects (AEs) happening throughout the study period, whether reported spontaneously by the participants or observed by the researchers, will be recorded and categorized as needling-related AEs. Common adverse events associated with acupuncture include persistent post-needling pain, dizziness, subcutaneous hematoma, infection, etc. Serious adverse events will be reported and handled according to relevant regulations within 24 h.

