### Statistical analysis

#### Clinical data analysis

Statistical analysis will be conducted utilizing SPSS 20.0 (IBM Corporation, Armonk, NY, United States), a software package to analyze statistical data. Statistical significance was determined at the 0.05 level (two-tailed). The intention-to-treat (ITT) analysis will be employed as the primary analysis for all patients, and missing data were filled in using the last observation carried forward (LOCF). A supplementary analysis will be conducted using the adherence protocol analysis (PP).

The categorical data will be described using frequencies and percentages. The proportion of patients with progression ≥0.5 grades compared to the baseline of H–Y staging, and adverse events were analyzed using the chi-squared test. The initial step in the analysis of continuous data is to assess their normality. The data are described using mean ± standard deviation or median (interquartile range). Within-group comparisons are conducted using either paired *t*-tests or Wilcoxon signed-rank tests, while between-group comparisons are carried out using independent samples *t*-tests or Mann–Whitney *U* tests. HAMD-17, QIDS-SR, UPDRS-III, and PDQ-39 were analyzed using either repeated-measures ANOVA or a generalized linear mixed model based on repeated measurements.

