One potential limitation of this study is that, due to the practicalities of acupuncture treatment, blinding for acupuncturists cannot be implemented. A further limitation of this study is that we were unable to control medication use. To address this limitation, we had a professional physician conduct a systematic specialty assessment before enrolling patients. It was anticipated that no routine medication adjustments would be necessary for the duration of the next 3 months.

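### The safety section classes every adverse effect in the 48 weeks as needling-related, so the needling-related rate would be overstated in both arms

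*Protocol article*

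**What the plan says.** The rule is in the protocol article under Safety assessments. Any adverse effect during the study period, "whether reported spontaneously by the participants or observed by the researchers, will be recorded and categorized as needling-related AEs". The section gives no other category and no step for judging cause. It goes on to list typical acupuncture events (pain after needling, dizziness, haematoma, infection) and requires serious events to be reported within 24 hours.

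Under Clinical data analysis, H–Y progression "and adverse events were analyzed using the chi-squared test". The word needling-related does not appear there.

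The study period is set out in the Abstract: "Data will be collected at baseline, at the end of the 12-week treatment period, and during the 12-week and 36-week follow-up". Table 1 places these times at weeks 0, 12, 24 and 48. The Interventions section confines the 36 sessions to the first 12 weeks. The Discussion names efficacy and safety together as principal objectives.

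**The concern.** The safety sentence states a rule; it does not merely leave a detail out. Followed literally, it leaves no way to class an event as unrelated to needling. A fall, a drug side effect, a deepening of the depression or an illness months after the last session would all be reported as harm from needling.

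At stake is the needling-related adverse event rate in each arm, which is the figure a reader would take as the safety profile of acupuncture. The two arms are needled differently: 0.30 mm needles at 8 to 15 mm with manipulation, against 0.18 mm needles at 2 to 4 mm without. Harm from needling could therefore really differ between them, and a label that sweeps in everything else makes such a difference harder to see.

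**Working it through.** The plan gives no adverse event figure to reproduce, so the check compares the rule with the rest of the article and then follows its effect on a rate.

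**Time.** Sessions: 3 per week × 12 weeks = 36, all in weeks 0 to 12. Study period: 12 + 36 = 48 weeks. Share with no trial needling scheduled: 36/48 = 75%. The rule covers all 48 weeks.

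**Cause.** The article itself names sources of events other than needling:
- Drugs. The inclusion criteria require a fixed anti-Parkinson drug plan. The Introduction lists impulse control disorder and sleep dysfunction as side effects of dopamine agonists. The Discussion adds: "A further limitation of this study is that we were unable to control medication use".
- The depression itself. The Introduction treats suicidal tendencies as part of depression in Parkinson's disease and says that "a considerable number of patients die by suicide".
- Disease progression. H–Y stage is expected to worsen in some patients, since its progression at week 48 is a secondary outcome.

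**Effect on the rate in one arm of 44.** Let r be the patients with at least one event truly caused by needling, and u the patients whose events all have other causes.
- True needling-related rate: r/44.
- Rate under the rule: (r + u)/44.
- Excess: u/44, which cannot be negative.

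Each such patient adds 1/44 = 2.3 percentage points to that arm's rate. The article gives no basis for u, so no total is offered.

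**Effect on the contrast between arms.** Write A for acupuncture and S for sham. Under the rule the difference is (r_A − r_S)/44 + (u_A − u_S)/44. If u_A = u_S = u, the difference is unchanged, but the ratio (r_A + u)/(r_S + u) lies nearer 1 than r_A/r_S.

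**Effect on the planned test.** The chi-squared test is stated for adverse events without the label. The number of patients with any event in an arm is r + u whether or not events are called needling-related, so the all-event test gives the same result.

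**The case against.** The strongest reply is that this is condensed wording. The article speaks of adverse effects, the next sentence lists events typical of acupuncture, and the intended meaning may be that events are classed as needling-related or not. That is plausible, but the sentence does not say it, and staff following it would have only one class. Correcting it is right on either reading.

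Two further objections stand and limit the point. The rule applies equally to both arms, because sham patients are needled too, so it does not by itself favour one arm. And the article does not say that worsening depression is logged as an adverse event at all; depression is the efficacy outcome. The point therefore rests on unrelated events in general, with mood as one example.

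A reader might infer that the label distorts the planned safety test. The documents do not support that: the test is on adverse events, and relabelling does not change their number.

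A reader might also infer an error in the schedule, because no depression scale falls between weeks 0 and 12 ("depression assessments and MRI scans will be performed immediately after baseline and intervention completion") in patients excluded if "currently taking or have taken traditional antidepressants in the past 2 weeks". But the Abstract, Study design, Table 1 and the secondary outcomes agree on this schedule. Entry is limited to HAMD-17 ≤24, patients attend three times a week, and mood-safety procedures may sit in the full protocol. An interim QIDS-SR would correct no error. It would also need a cut-off the article does not give and a clinically competent reader, and it could lead to antidepressant starts that affect the week-12 primary outcome. It is a matter of preference and forms no part of this point.

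**Conclusion.** The classification rule is wrong as written and should be corrected. Taken literally, it makes the needling-related rate equal to the all-event rate, so the error can only run upwards. It affects each arm in which at least one patient has only events of other causes. That this will happen in both arms over 48 weeks is an assumption, though a mild one in patients aged 50 to 75 with Parkinson's disease on continuing drug treatment.

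The size of the excess cannot be stated from the documents. The all-event chi-squared comparison, the HAMD-17 primary outcome and the sample size are untouched. The conclusion assumes that the sentence reflects how events will be classed; if the full protocol contains a causality step, only the article's wording is at fault.

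**What to change.** Replace the sentence under Safety assessments with, for example: 'All adverse events, including worsening depression and suicidal thoughts, will be recorded; relation to needling (acupuncture or sham) will be judged separately for each event.' Report two tables by arm: all adverse events, and needling-related adverse events. Keep the chi-squared test on all adverse events as planned.

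Because the acupuncturists know the allocation, the judgement is better made by someone else on the study team. Recruitment is under way, so events already recorded should be classified in the same way.

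The cost is one sentence in an amendment and a little causality assessment per event, including a review of those already on file. No visit, outcome or sample size changes.

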**Discussion:**

This study hypothesized that acupuncture may treat DPD by restoring pathological alterations in brain neural activity. The findings will provide scientific evidence for acupuncture in the treatment of early PD with mild to moderate depression.

**Ethics and dissemination:**

This clinical trial has been approved by the Medical Ethics Committee of the Beijing Hospital of Traditional Chinese Medicine (Approval No. 2023BL02-013-01). This trial has been registered with the Chinese Clinical Trials Registry (Registration No. ChiCTR2300069310). The results will be published in a peer-reviewed academic journal.

**Clinical trial registration:**

https://www.chictr.org.cn/, identifier ChiCTR2300069310.

## Introduction

Parkinson’s disease (PD) is a neurodegenerative disease characterized by bradykinesia, rest tremor, and muscle stiffness (1, 2). In addition to symptoms of movement disorders, PD patients also experience various non-motor symptoms, such as depression, rapid eye movement sleep behavior disorder, pain, etc. (3). Approximately 35 to 50% of PD patients will experience depression, which often persists (3, 4).

Depression is a common non-motor symptom that occurs in patients with all stages of PD (5). A meta-study showed that 17% of PD patients in clinical practice suffer from severe depression, 35% have clinically significant depressive symptoms (6), and a portion of patients have suicidal tendencies (7). Depression is one of the biggest factors affecting the quality of life of PD patients, especially female PD patients (8).

In addition, depression is often a sign of other symptoms of PD and has diagnostic value. For early PD patients, depression may be one of the early signs before the onset of motor symptoms (9). For patients with advanced PD, depression may be one of the early signs of more severe non-motor symptoms (dementia, falls, disability) in the later stages (10, 11). Secondly, depression itself can seriously affect the quality of life of Parkinson’s disease patients. Patients with Parkinson’s disease and depression often experience significant negative emotions such as shame, suicidal tendencies, low morale, and despair, and a considerable number of patients die by suicide (12). These negative emotions seriously affect the quality of life (QoL) of Parkinson’s disease patients and significantly impact prognosis (13, 14). Therefore, developing a new treatment plan for Parkinson’s disease with depression has practical significance and can improve the quality of life of patients.

For a long time, research on the tolerance, safety, and efficacy of antidepressants in Parkinson’s disease patients has been very limited (15, 16). A study has found that dopamine agonists may alleviate depression in early Parkinson’s disease (17). Nevertheless, dopamine agonists have side effects on impulse control disorder and sleep dysfunction. Tricyclic antidepressants (TCAs) and selective serotonin reuptake inhibitors (SSRIs) have been subjected to a limited number of trials to assess their therapeutic efficacy in the treatment of DPD. The overall results are positive, but the evidence is not sufficient (15, 18, 19). However, TCA drugs have side effects such as drowsiness, dry mouth, urinary retention, constipation, cognitive impairment, hypotension, and abnormal cardiac conduction, which limit their application in the treatment of DPD. Although SSRI drugs can improve depression in DPD patients, they can worsen their motor symptoms (20). There is a lack of research on SNRI drugs for treating DPD, and there is insufficient evidence to prove the efficacy of such drugs in treating DPD (21). The above-mentioned antidepressants may have a potential tendency to worsen motor or non-motor symptoms in DPD, which encouraged research on non-pharmacological treatment of DPD. Non-pharmacological treatments can be used independently or in conjunction with conventional antidepressants. PD patients often express interest and experience positive emotions towards this treatment strategy (22). Thus, it’s important to research non-pharmacological treatment of DPD.

The efficacy of acupuncture in the treatment of depression has been demonstrated in clinical trials. A randomized controlled trial demonstrated that acupuncture could enhance the effectiveness of antidepressant medications while decreasing their side effects (23). Research shows that acupuncture can alleviate depression by improving neural plasticity, reducing brain inflammation, regulating neuroendocrine, and regulating the expression of brain-derived neurotrophic factors (24–28). Nevertheless, the effect of acupuncture on DPD has not been studied. A study demonstrated the atrophy of the dorsal portion of the anterior cingulate cortex (ACCx) in DPD (29). One experiment in Rat shows acupuncture will increase the activities of glutamatergic neurons in the ACCx and serotoninergic neurons in the DRN, thus significantly alleviating both mechanical allodynia and anxiety-like behaviors (30). Experimental research is needed to verify this hypothesis. Thus, acupuncture may alleviate DPD by changing the brain’s anatomy and function. This hypothesis has to be verified by experimental research.

Pathophysiological studies have found that there are certain differences in the pathogenesis between DPD and primary depression. DPD is a holistic disorder involving the interplay of discrete brain regions rather than a focal structural or functional disorder (15). A meta-study summarized the current research on the functional brain mechanisms of PD with depression and found that its pathogenesis was associated with the cingulate gyrus, supplementary motor function areas, and cerebellar BOLD signaling (25). Therefore, neuropsychological tests combined with functional magnetic resonance imaging (fMRI) may be a better evaluation criterion. Using fMRI to examine the changes of brain function can better observe the clinical efficacy of acupuncture and moxibustion and explore its therapeutic mechanism.

## Methods

### Study design

The methodological framework for this project was developed based on the Consolidated Standards of Reporting Trials (CONSORT) statement for non-pharmacological interventions. The protocol was approved by the Medical Ethics Committee of the Beijing Hospital of Traditional Chinese Medicine (2023BL02-013-01) and is registered with the Chinese Clinical Trial Registry (Registration No. ChiCTR2300069310).

This trial is a 1:1 randomized, single-blind, and placebo-controlled study with two parallel groups, involving patients with early PD with mild to moderate depression. The study is designed to evaluate the effect and neural mechanism of acupuncture treatment on depression and motor symptoms after a 12-week intervention period. As shown in Figure 1, depression assessments and MRI scans will be performed immediately after baseline and intervention completion. The enrollment schedules, interventions, and assessments are summarized in Table 1.

**Figure 1 fig1:**
[figure not shown]
Flow chart.

**Table 1 tab1:** Study period.

Items	Screening	Baseline	Treatment	Follow-up	
Timepoint	Week 1	Week 0	Week 12	Week 24	Week 48
Enrolment					
Eligibility screen	X				
Informed consent	X				
Intervention					
Acupuncture (*n* = 44)					
Sham acupuncture (*n* = 44)					
fMRI scan					
Acupuncture		X	X		
Sham acupuncture		X	X		
Assessment					
HAMD-17		X	X	X	X
UPDRS-III		X	X	X	X
QIDS-SR		X	X	X	X
PDQ-39		X	X	X	X
H-Y		X			X

### Participants

The methodology framework for this project is as follows: the study will be conducted in Dongcheng District, Beijing. The patient with DPD will be recruited from the outpatient department of the Acupuncture Center at Beijing Hospital of Traditional Chinese Medicine and the outpatient department of Neurology of Peking Union Medical College Hospital. To improve residents’ understanding of the trial, a popular science lecture on acupuncture for PD will be held on 11 April (World Parkinson’s Day). Additionally, posters will be displayed at the outpatient clinic of the Acupuncture Center at Beijing Hospital of Traditional Chinese Medicine. Furthermore, the trial advertisement will be posted on the official WeChat account of Beijing Hospital of Traditional Chinese Medicine. Patients interested in the clinical trial will be screened at Beijing Union Medical College Hospital using the inclusion/exclusion criteria. All patients who meet the inclusion criteria will receive an informed consent form that outlines the study objectives, design, procedures, benefits, and risks. Before the commencement of study procedures, subjects will be required to provide written informed consent. The diagnosis of DPD will be conducted following the diagnostic criteria for DPD outlined in the Guidelines for the Diagnosis and Treatment of Depression, Anxiety, and Psychotic Disorders in PD. The Parkinson’s Specialized Clinic at the Department of Neurology of Peking Union Medical College Hospital will assess the level of depression using the 17-item Hamilton Depression Rating Scale (HAMD-17 score >7 and ≤24). The Hoehn–Yahr Staging Scale is employed to evaluate the severity of PD (H–Y score ≤2.5), while the Mini-Mental State Examination (MMSE) is used to assess language and cognitive abilities (MMSE score >20). A Peking Union Medical College Hospital neurologist will fix a drug treatment plan.

